
### Study flow

The study flow is detailed in Figure 1. Firstly clinics will be randomized to group 1, 2 or 3. After participants are screened for eligibility based on the inclusion/exclusion criteria and provide written informed consent, they will undergo baseline physical function tests 12 weeks prior to the commencement of the intervention. At the completion of these tests, the investigator will explain and ask the participant to take home the combined questionnaire which will include the KDQOL, FAI, Boston Falls Calender and the modified falls efficacy scale. Participants will be asked to complete these questionnaires and return them at their next dialysis visit. Data obtained will be transcribed onto case record forms for entry into a specifically designed trial database. Data analysis will then be undertaken by an investigator who is blinded to the group intervention. The data collection plan is detailed in Table 1.

### Study withdrawal

Participants can withdraw from the intervention at any stage, effective immediately, without affecting clinical care as documented and explained at time of consent. Participants who withdraw will be invited to consent to follow-up testing for the remainder of the trial to enable an intention-to-treat data analysis.

### Sample size calculation

The 30 second sit-to-stand test is the most clinically meaningful primary outcome measure and was used in the sample size calculations for this study. It is clinically meaningful because many people with chronic kidney disease on hemodialysis have great difficulty simply getting out of bed or out of a chair. This inability to stand quickly from a chair is associated with their poor muscle condition [24,25] and renal bone disease [26]. Likely effect sizes have been estimated from the sit-to-stand test data from two previous studies [27,28]. In Cappy et al. [27] the effect sizes (d) for the three, six, and twelve-month changes in reps were 0.65, 1.12, and 2.39, respectively. In McDonald et al. [28] the effect size (d) for the 12-week change was 2.42. We chose the most conservative findings with the lowest effect size (Cappy’s 3-month change: d = 0.65) for the sample size calculations. Cappy et al. [27] demonstrated a medium-sized effect for the effect of a physical activity intervention (d = 0.65), alpha was set at p < 0.0125 (an adjustment was made to the typical level of p < 0.05 for judging statistical significance in these types of studies, because there will be a test at each of four time points and we wish to control experiment wise error). Power was set at .80. Based on our previous pilot work a 30% attrition rate over 12 months is expected [10]. A design effect (DE = 1.25) was included to account for clustering (ICC = .029, m = 9.73). The intra-cluster correlation coefficient was estimated from prior work with people with diabetes in primary care practices: ICC = .029 [29]. We will require 15 clusters, with each cluster representing one hemodialysis clinic. Based on these assumptions, 180 participants will need to be recruited for the study. Thus in each of the 15 clinics we will need to recruit a minimum of 12 participants.

### Statistical analyses

For the primary outcome measure there will be five data collection points, one every 12 weeks as follows: Time 1 (0 weeks, no intervention), Time 2 (12 weeks, Group 1 commences intervention), Time 3 (24 weeks, Group 2 commences intervention), Time 4 (36 weeks, Group 3 commences intervention) and Time 5 (48 weeks, intervention completed). This design characteristic means analyses will occur at three time points (Time 3 to Time 5) with the data at each of these time points compared with baseline data. Three tests means that the standard α value (p < 0.05) will need to be divided by three (a Bonferroni adjustment): α = .05/3 = .0167. Initially, analyses of variance with baseline scores as co-variates (ANCOVAs) will be the method of analysis. In addition, to account for the clustering effect, generalised linear mixed models with random effects will be used to analyse differences between control period and intervention period.

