## Methods

### Study design and setting

This study will use a stepped wedge cluster randomised controlled trial design. This method is a form of randomised controlled trial where randomisation occurs while still allowing all participants the opportunity to undertake a period of intervention [12]. In this study, the randomisation will occur at a clinic level rather than individual participant level. Participants will be recruited from 15 community satellite hemodialysis clinics across five healthcare organisations in Melbourne, Australia. Each clinic will represent a cluster unit. The stepped wedge design will consist of three groups each containing five randomly allocated cluster units. The first group will receive 36 weeks of the AEP-coordinated exercise intervention, the second group will receive 24 weeks, and the third group will receive 12 weeks. The study will be conducted over a 48 week period, incorporating a 12 week pre-intervention period. The study design was reviewed by the Australian New Zealand Clinical Trials Registry (ANZCTR), approved and registered as ACTRN12612001223820 on the 19th November, 2012.

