### Data collection

Baseline data (Time 1) for all participants will be collected 12 weeks prior to the commencement of the intervention for the first group. The second round of data collection (Time 2) will be conducted 12 weeks later and participants from the five clinics randomised to receive 36 weeks of intervention (Group 1) will commence the exercise intervention. The third round of data collection (Time 3) will be conducted 12 weeks later and participants from the five clinics randomised to receive 24 weeks of intervention (Group 2) will commence the exercise intervention. The fourth round of data collection (Time 4) will be conducted 12 weeks later and participants from the five clinics randomised to receive 12 weeks of intervention (Group 3) will commence the exercise intervention. The final round of data collection will be conducted in the week after the intervention ceases in all clinics, 48 weeks after the first data is collected (Time 5) (Table 1).

**Table 1 T1:** Outcome measures

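### The Time 5 test of the primary outcome cannot compare intervention with no intervention, because every clinic has been exposed by then; it should be relabelled as a comparison of durations

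*Protocol article*

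**What the plan says.** Study design and setting: "The stepped wedge design will consist of three groups each containing five randomly allocated cluster units", and "The first group will receive 36 weeks of the AEP-coordinated exercise intervention, the second group will receive 24 weeks, and the third group will receive" the shortest course, of 12 weeks.

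Data collection staggers the starts at Times 2, 3 and 4. At Time 4, "participants from the five clinics randomised to receive 12 weeks of intervention (Group 3) will commence the exercise intervention". Of Time 5 it says: "The final round of data collection will be conducted in the week after the intervention ceases in all clinics". The Statistical analyses section repeats this schedule: "Time 4 (36 weeks, Group 3 commences intervention) and Time 5 (48 weeks, intervention completed").

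The same section then draws the number of tests from the design: "analyses will occur at three time points (Time 3 to Time 5"), each of them set against baseline. It divides 0.05 by three, names ANCOVA with the baseline score as covariate as the initial method, and adds generalised linear mixed models with random effects, to allow for clustering and to contrast the control period with the intervention period. It does not say which analysis takes precedence, or that Time 5 answers a different question from Times 3 and 4.

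The Background states the objective as the effect of the programme on physical function and hypothesises that the programme improves it. Neither statement mentions duration.

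**The concern.** The three tests are presented as one family, with one correction and one method. A reader would take each to address the primary objective. At Times 3 and 4 some clinics have started and others have not, so a baseline-adjusted comparison between groups is a randomised comparison of programme with no programme. At Time 5 it is not.

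Two misreadings are possible. A significant Time 5 result could be reported as efficacy when it shows that longer exercise does better than shorter, or that scores changed over 48 weeks for any reason. A non-significant result could be reported as lack of effect when all three durations work about equally well. In addition, one third of the alpha goes to a test that does not address the stated hypothesis.

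**Working it through.** **1. The plan's own figure.** Bonferroni for three tests: 0.05/3 = 0.0167. This reproduces.

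**2. Exposure at each occasion.** Weeks on intervention = occasion week minus start week (12, 24 and 36 for Groups 1, 2 and 3), or zero if negative.

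| Occasion | Week | Group 1 | Group 2 | Group 3 | Unexposed clinics |
|---|---|---|---|---|---|
| Time 1 | 0 | 0 | 0 | 0 | 15 |
| Time 2 | 12 | 0 | 0 | 0 | 15 |
| Time 3 | 24 | 12 | 0 | 0 | 10 |
| Time 4 | 36 | 24 | 12 | 0 | 5 |
| Time 5 | 48 | 36 | 24 | 12 | 0 |

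Only Times 3 and 4 have both exposed and unexposed clinics.

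**3. What each reading of the Time 5 test can estimate.**
- *Between groups at Time 5.* The exposed/unexposed indicator is 1 in all three groups. A model with an intercept and a treatment term has rank 1 for 2 parameters, so the treatment effect is not estimable. At Time 3 the same model has rank 2.
- *Time 5 against baseline.* With Times 1 and 5 only, a model with intercept, time and treatment has rank 2 for 3 parameters. Treatment cannot be separated from 48 weeks of change.
- *All five occasions.* A model with an intercept, four time effects and a treatment term has full rank 6. Time 5 data are usable here because the earlier occasions supply the control data.

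**4. What a Time 5 between-group difference might be.** This depends on how the effect grows. If it is complete by 12 weeks and then constant, the expected difference is 0. The Sample size calculation section, however, cites d = 0.65, 1.12 and 2.39 at three, six and twelve months. Taking 12 and 24 weeks as roughly three and six months, Group 2 against Group 3 would differ by about 1.12 − 0.65 = 0.47, and Group 1 against Group 3 by more. A non-zero difference is therefore quite possible, but it would be a duration effect.

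**5. Power released at Time 3.** Comparison of 5 with 10 clinics (1:2), d = 0.65, two-sided (sidedness is not stated, so this is assumed). Design effect = 1 + (m − 1) × 0.029, with m = completers/15. Effective N = completers/design effect. Non-centrality = 0.65 × √(effective N × 2/9). Power is from the non-central t with completers − 2 degrees of freedom.

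- *Full 30% loss:* 180 × 0.70 = 126; m = 8.4; design effect 1.2146; effective N 103.7; non-centrality 3.12. Power is 0.755 at 0.0167 and 0.802 at 0.025. A normal approximation with the protocol's rounded design effect of 1.25 gives 0.753 and 0.798.
- *Half that loss by week 24* (assuming a linear rate): 180 × 0.85 = 153; m = 10.2; design effect 1.2668; effective N 120.8; non-centrality 3.37. Power is 0.827 and 0.864.
- *126 completers, assumed baseline correlation 0.5* (non-centrality divided by √0.75): 3.60. Power is 0.879 and 0.908.
- *153 completers, same correlation:* 3.89. Power is 0.927 and 0.947.

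The gain is 0.047, 0.037, 0.029 and 0.020 respectively, or about 2 to 5 points.

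**The case against.** The strongest reply is that the control-versus-intervention contrast is already planned. The mixed model in the same section makes it, Time 5 data properly enter that model, and a condensed article may leave the time terms to a fuller plan. That stands, and it limits the point. It does not remove it: the per-time ANCOVAs are named as the initial method, the alpha is set for them, and the mixed model is an addition. Which tests are done, when and at what alpha is stated, not left open.

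A second reply is that a baseline-adjusted ANCOVA is the natural reading of the phrase "with the data at each of these time points compared with baseline data", and that at Time 5 this is a valid randomised comparison of 36, 24 and 12 weeks. That also stands. But the article states no duration hypothesis and does not label the test as one.

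Several stronger conclusions might be inferred, and the documents do not support them:
- *That the primary analysis as a whole lacks a control.* Times 3 and 4 have concurrent randomised controls, and the mixed model uses the control periods.
- *That the Time 5 difference must be zero.* This needs a plateau at 12 weeks, against the cited effect sizes that rise with duration.
- *That drift biases the result by a known amount.* No drift figure is given. The Background expects decline without exercise, which would work against the programme, while retest practice and selective dropout could work the other way. The net direction is unknown, and this matters only under the before-after reading.
- *That assessor blinding fails at Time 5.* Blinding to group still protects a comparison of durations. It gives no protection only under the before-after reading.
- *That the extra test inflates type I error.* Bonferroni over three tests controls it.

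**Conclusion.** The point holds for the Time 5 per-occasion test alone. One of three alpha-adjusted tests of the primary outcome cannot estimate the effect of the programme against no programme, under either reading of the text. This follows from the roll-out schedule and needs no outside assumption. Strictly, at Time 5 the clinics have all been exposed rather than being still on the programme, since measurement follows in the week after it ends; the conclusion is the same.

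The main consequence is interpretive: a Time 5 result of either sign may be misreported as evidence for or against efficacy. The power cost is modest, about 2 to 5 points at Time 3, and that range rests on assumed attrition by week 24 and an assumed baseline correlation. It merits correction because it concerns the primary outcome and is cheap to put right.

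**What to change.** Preferred: make the mixed model already planned the single primary test, contrasting control with intervention periods over all five occasions, with time effects stated explicitly. No alpha is then divided between occasions, and Time 5 data are used where they are informative.

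Alternative, if per-occasion tests are kept: test intervention against control only at Time 3 (Group 1 against Groups 2 and 3) and Time 4 (Groups 1 and 2 against Group 3), each at 0.05/2 = 0.025.

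In either case:
- relabel Time 5 as a secondary or descriptive comparison of 36, 24 and 12 weeks, and state that it will not be reported as efficacy;
- clarify that comparison with baseline means adjustment for the baseline score, not a before-after test;
- align the number of tests with the Sample size calculation section, which uses four tests and an alpha of 0.0125 where the analysis section uses three and 0.0167.

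The cost is a change of wording before the data are analysed. No new participants, visits or measurements are needed.

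### Holm's procedure would give the same experiment-wise error control as the planned single-step Bonferroni and could only add rejections: a cheap improvement, not an error

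*Protocol article*

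**What the plan says.** Under Statistical analyses, the protocol article states that "analyses will occur at three time points (Time 3 to Time 5"), with baseline scores as covariates. For those tests the standard level "will need to be divided by three (a Bonferroni adjustment"), written out as "α = .05/3 = .0167". The same section adds mixed models that compare control with intervention periods.

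Under Sample size calculation, the reason for adjusting is given as "there will be a test at each of four time points and we wish to control experiment wise error". There "alpha was set at p < 0.0125" and "Power was set at .80". The effect used is d = 0.65, the three-month change in one earlier study and the lowest value quoted. That study's six- and twelve-month values are 1.12 and 2.39. A second study's 12-week value is 2.42.

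The two sections therefore disagree on the number of tests (four or three), but both use a single-step Bonferroni level.

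**The concern.** Single-step Bonferroni holds each test to .0167 whatever the other two show. Holm's procedure compares the smallest p-value with .05/3, the next with .05/2 and the largest with .05, and stops at the first failure. The experiment-wise error stays at or below .05 under any dependence between the tests, and that is the only kind of control the article asks for.

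What is at stake is which time points can be claimed, not whether the trial can succeed at all. With p = .001, .010 and .022, for example, Bonferroni claims two time points and Holm claims three, inside the same 5% budget.

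**Working it through.** **1. The plan's own figures.** .05/3 = .0167 is exact. For the sample size, take a two-sided test (sidedness is not stated), two equal groups and d = 0.65:

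- At .0167: n per group = 2 × (2.394 + 0.842)² / 0.65² = 49.6, so 50. Then 100 × 1.25 / 0.7 = 178.6, so 179, which agrees with 180.
- At .0125: 53 per group by the normal approximation gives 106 × 1.25 / 0.7 = 189.3, so 190. The t-based 55 per group, with attrition applied as a multiplier, gives 110 × 1.25 × 1.3 = 178.75, so 179.

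The total of 180 can thus be reached from either level, depending on the convention used.

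**2. Why Holm cannot reject less.** Every Holm level (.0167, .025, .05) is at least .0167. If a p-value is at or below .0167, so are all smaller ones, so Holm reaches it and rejects it. The first step is identical to Bonferroni, so the chance of at least one rejection is identical.

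**3. Time 3 as 5 against 10 clinics.** By the data collection schedule, at Time 3 Group 1 has had 12 weeks of exercise and Groups 2 and 3 have had none. The article does not write out this contrast; it is inferred. Inputs are 60 against 120 recruited, 30% attrition and d = 0.65.

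- With the stated design effect of 1.25, effective numbers are 60 × 0.7 / 1.25 = 33.6 and 120 × 0.7 / 1.25 = 67.2. SE = √(1/33.6 + 1/67.2) = .211 and d/SE = 3.08.
- With the design effect for 126 completers (8.4 per clinic), 1 + 7.4 × .029 = 1.2146. SE = √(1.2146 × (1/42 + 1/84)) = .208 and d/SE = 3.12.

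Power is Φ(d/SE − z), with z = 2.394, 2.241 and 1.960:

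| Level for Time 3 | Design effect 1.25 | Design effect 1.21 |
|---|---|---|
| .0167 | .753 | .766 |
| .025 (one other test already rejected) | .798 | .810 |
| .05 (both others already rejected) | .868 | .877 |

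The last two rows are not Holm's power in themselves. They apply only once other tests have been rejected.

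**4. Holm's actual power at Time 3.** Three correlated z statistics were simulated (correlation 0 to .8, the same SE for all three tests; both are assumptions). The effects at Times 4 and 5 are also assumptions.

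| Effects at Times 3 / 4 / 5 | Design effect 1.25: Bonferroni, Holm | Design effect 1.21: Bonferroni, Holm |
|---|---|---|
| .65 / 1.12 / 1.12 | 75%, 87% | 77%, 88% |
| .65 / .65 / .65 | 75%, 81–84% | 77%, 82–85% |
| .65 / 1.12 / 0 | 75%, 80% | 77%, 81% |
| .65 / 0 / 0 | 75%, 75% | 77%, 77% |

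At design effect 1.25 the simulated chance of at least one rejection was the same under both rules in every row.

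**5. Sensitivity.**

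- The 30% attrition is a 12-month figure, and Time 3 falls at week 24. With an assumed 15% loss (51 against 102, design effect 1.267), power is .835 at .0167, .870 at .025 and .920 at .05.
- With two equal groups (50.4 effective each), Bonferroni gives .808. Holm gives .85 to .90 when at least one other effect is real.

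**6. Error.** With all three effects null, experiment-wise error was .035 to .049 under both rules. With two real effects and one null, the null test's own error was .017 under Bonferroni and .038 to .046 under Holm.

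**The case against.** The strongest reply is that nothing here is wrong. Bonferroni is valid, the level is computed correctly, the article gives its reason, and a Bonferroni level is already built into the sample size. That stands, and it limits the point to an optional gain in efficiency.

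A reader might infer that power is given away for nothing. That goes too far. It is true of the experiment-wise bound only. Bonferroni also holds each single test at .0167 and yields simple simultaneous intervals, and Holm does neither.

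A reader might also infer that the trial was sized for Time 3 and that the loss falls there. The article does not say so. It takes 0.65 as the most cautious value quoted and applies it to a family of tests. At Time 5 every group has been treated (36, 24 or 12 weeks), so a between-group contrast there could be the weakest of the three. The other study's 12-week effect of 2.42 gives d/SE of about 11.6 on an SE of .208, so power at .0167 would be essentially 100% and Holm would add nothing at Time 3.

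Nor do the figures show that Bonferroni leaves the trial below its planned 80%. That happens for 5 against 10 clinics with the full 30% loss at week 24, but not with 15% loss or two equal groups.

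Finally, the hypothesis is that the program improves function, not that it does so by a given week, and the mixed-model comparison of periods is untouched. This lowers the stakes. It does not remove the advantage for the time-point claims.

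**Conclusion.** The point holds as a cheap improvement. For the aim the article states, Holm gives the same .05 experiment-wise control and never rejects less.

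On the inferred 5 against 10 contrast at Time 3 with d = 0.65, power goes from about 75–77% to about 80–88% when at least one other time point has a real effect of the sizes assumed (.65 or 1.12). It does not rise when neither has one. The chance of at least one significant test does not change.

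These sizes rest on two-sided tests, 30% loss already reached at week 24, and the assumed later effects and correlations. Which time point gains depends on contrasts that the article does not write out.

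**What to change.** Replace the single-step rule with one sentence: the p-values of the planned time-point tests will be ordered and judged by Holm's procedure at an experiment-wise two-sided level of .05 (.0167, .025, .05 for three tests). First reconcile the three-test and four-test statements. If four tests are kept, the levels are .05/4 = .0125, then .0167, .025 and .05.

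No new data or participants are needed, but the rule should be fixed before outcome data are seen. There are two costs. A single true-null test is no longer held at .0167, and its error can approach .05 when the other effects are real. Simple simultaneous confidence intervals are also lost, so report unadjusted 95% intervals, labelled as such, beside the Holm decisions.

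### ANCOVAs with no stated clinic term are named as the method of analysis, the cluster-adjusted mixed model is only an addition, and no rule says which decides

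*Protocol article*

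**What the plan says.** All references are to the protocol article.

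- **Study design and setting:** "the randomisation will occur at a clinic level rather than individual participant level". The layout is three groups of five clinics.
- **Sample size calculation:** "A design effect (DE = 1.25) was included to account for clustering", from an ICC of 0.029 and 9.73 participants per clinic. In the same section "alpha was set at p < 0.0125", justified by four tests.
- **Statistical analyses, tests and alpha:** "analyses will occur at three time points (Time 3 to Time 5) with the data at each of these time points compared with baseline data". For these three tests the level is "α = .05/3 = .0167".
- **Statistical analyses, methods:** "Initially, analyses of variance with baseline scores as co-variates (ANCOVAs) will be the method of analysis". The next sentence reads "In addition, to account for the clustering effect, generalised linear mixed models with random effects will be used", and applies these models to the difference between control and intervention periods. It gives no alpha for them and does not rank the two approaches.

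**The concern.** When clinics are randomised, patients of one clinic share its staff, case mix and assessor habits. The uncertainty of a group comparison then depends on variation between clinics as well as between patients. An ANCOVA on participants without a clinic term leaves the between-clinic part out, so its standard errors and p-values are too small. The wording points that way. The mixed model is introduced for the stated purpose of handling clustering, which implies that the ANCOVAs do not handle it. The sample size section, by contrast, pays for clustering with 25% more participants.

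The two analyses also answer different questions: three contrasts at separate time points, and one contrast of control with intervention periods. With no rule on which decides, a significant unclustered ANCOVA beside a non-significant mixed model could be reported as success without departing from the published plan.

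**Working it through.** **1. The plan's own figures.** The design effect is 1 + (m − 1) × ICC = 1 + 8.73 × 0.029 = 1.253, which agrees with the stated 1.25. For d = 0.65, 80% power and two-sided alpha 0.0125 (sidedness is not stated), a two-sample t-test needs 55 per arm. Then 110 × 1.25 × 1.30 = 178.75, close to the stated 180. At alpha 0.0167, the normal formula gives 50 per arm and 100 × 1.25 / 0.70 = 178.6, which fits as well. So clustering is built into the 180, but the 180 does not reveal which alpha the trial uses.

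**2. Simple bound: baseline adjustment removes no clinic variance.** The two-sided critical value at 0.05/3 is z = 2.394. A test that ignores a design effect DE has true size 2 × (1 − Φ(2.394/√DE)).

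- m = 8.4 (12 × 0.70 after attrition): DE = 1.215, size 0.030
- m = 9.73: DE = 1.253, size 0.0325
- m = 12: DE = 1.319, size 0.037

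**3. Allowing for the baseline covariate.** An ANCOVA partly removes clinic differences that were already present at baseline. Let r be the correlation of a participant's baseline and outcome scores, and p the share of clinic variance that persists between visits. The article gives neither. The ICC left after adjustment is approximately

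0.029 × (1 + r² − 2rp) / (1 − r²),

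which for p = 1 reduces to 0.029 × (1 − r)² / (1 − r²). With 8 participants per clinic:

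| p | r | residual ICC | DE | true size (nominal 0.0167) |
|---|---|---|---|---|
| 1 | 0.5 | 0.0097 | 1.068 | 0.021 |
| 1 | 0.7 | 0.0051 | 1.036 | 0.019 |
| 0.8 | 0.5 | 0.0174 | 1.122 | 0.024 |
| 0.8 | 0.7 | 0.0210 | 1.147 | 0.025 |
| 0 | 0.5 | 0.0483 | 1.338 | 0.039 |
| 0 | 0.7 | 0.0847 | 1.593 | 0.058 |

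Larger clinics give larger values.

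**4. Simulation** of baseline-adjusted ANCOVA, 15 clinics of 8, ICC 0.029, r 0.5 to 0.7 (approximate figures):

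| clinic effects | per test (nominal 0.0167) | family-wise (nominal 0.05) |
|---|---|---|
| 80–100% persistent | about 0.02–0.03 | about 0.054–0.074 |
| all period-specific | about 0.04–0.07 | about 0.12–0.17 |

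The top of the period-specific range lies above the formula, which covers a two-group contrast. When Time 5 is tested across all three groups, the inflation there is greater.

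**5. Controls.** At ICC 0 the simulated family-wise error was 0.044, so clustering causes the excess. In a simulation with the ICC placed on the baseline-adjusted residuals, a cluster-level analysis at ICC 0.029 held 0.017 to 0.019 per test.

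**The case against.** The strongest reply is that clustering is planned for. The sample size carries a design effect, and the mixed model targets the control-versus-intervention contrast that a stepped wedge is built to estimate. The article never labels the ANCOVAs primary, and their introduction as an initial step can be read as a preliminary to the mixed model. That the ANCOVAs work on individual scores is an inference from the absence of any clinic term. This much stands: a reader who concludes that the plan ignores clustering goes further than the text allows. It does not close the gap, because the article states the method, its order and its alpha, and leaves the deciding analysis open.

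A reader might also infer that the error rate simply doubles, from step 2 of the working. The documents do not support that as the headline. It assumes that baseline adjustment removes no clinic variance, and with persistent clinic effects the excess is small. Adding the three per-test errors gives only an upper bound on the family-wise error, because the tests share participants. The ICC itself is borrowed from people with diabetes in primary care, so its value here could be lower or higher.

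Nor is leaving Time 2 out of the tests an error. The Data collection section shows that no clinic has been exposed before that assessment, so there is no treatment contrast to test. Averaging Times 1 and 2 as the covariate would be an optional gain in efficiency.

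Finally, the exact form of a small-sample correction is detail that an article may leave to a fuller plan. It appears below as part of the remedy, and its absence is not a fault.

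**Conclusion.** The point holds in limited form. Followed as written, the plan gives its adjusted alpha to tests with no stated allowance for clinics, in a trial that randomises clinics. It adds the suitable model without saying that this model decides. The direction of the error is certain for any positive ICC left after adjustment; its size is not. At the plan's own ICC it runs from slight (per test about 0.02, family-wise about 0.054) to serious (about 0.07 and 0.17), depending on how far clinic effects persist between visits and on a within-person correlation assumed to be 0.5 to 0.7. The missing decision rule is a defect at any ICC, because two analyses of one primary outcome can disagree.

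**What to change.** - Name the mixed model as the single primary analysis of control versus intervention periods, with random effects for clinic and participant, fixed effects for time, and a small-sample correction suited to 15 clusters.
- Label the ANCOVAs supportive, or add a clinic term to them.
- State one alpha for the primary test. The Sample size calculation section uses 0.0125 for four tests and the Statistical analyses section 0.0167 for three; a single primary contrast needs no such split.
- Restate the power basis for the chosen model and alpha. The present 180 rests on a two-group calculation with a simple design effect, so this is more than a change of wording.

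No new data are needed. The cost is a revised power statement, a p-value somewhat less favourable than the unclustered ANCOVA would give, and more reliance on the model's assumptions about time and clinic effects.

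### The three time-point ANCOVAs take no account of clinic in a clinic-randomised trial, and the mixed model that does is given no priority over them, so the 5% experiment-wise error is not assured.

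*Protocol article*

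**What the plan says.** Under Study design and setting, "the randomisation will occur at a clinic level rather than individual participant level", with "three groups each containing five randomly allocated cluster units". The Sample size calculation recognises what follows from this: "A design effect (DE = 1.25) was included to account for clustering", using an ICC of .029 and 9.73 participants per clinic.

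The Statistical analyses section then sets three comparisons with baseline (Times 3, 4 and 5) and divides .05 by three to give .0167. The method comes next: "Initially, analyses of variance with baseline scores as co-variates (ANCOVAs) will be the method of analysis". The following sentence reads "In addition, to account for the clustering effect, generalised linear mixed models with random effects will be used", and directs those models at the difference between time under control and time under intervention. The section does not say which of the two analyses carries the primary conclusion.

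**The concern.** When clinics are randomised, the chance variation that matters is variation between clinics. A two-group comparison of 15 clinics has 15 - 2 = 13 degrees of freedom, however many patients are measured. An ANCOVA on individual patients with no clinic term uses the patient count instead, and reads part of the clinic variation as information.

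The wording indicates that the ANCOVAs are of this kind, because the mixed models are added for the stated purpose of handling clustering. Those models estimate a different contrast, so they do not correct the three time-point p-values or intervals.

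At stake is the purpose of the Bonferroni division. The protocol wants experiment-wise error held, but dividing .05 by three does that only if each test has its nominal size. Otherwise a chance difference between a few clinics could be reported as an exercise effect on the sit-to-stand test, with an interval that is too short.

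**Working it through.** **Inputs from the protocol.** 15 clinics in three groups of five; 180 participants, 12 per clinic; 30% attrition over 12 months; ICC .029; m = 9.73; three tests at .05/3 = .0167 (two-sided assumed).

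**The plan's own figure.** DE = 1 + (m - 1) × ICC = 1 + 8.73 × .029 = 1.253, which reproduces the stated 1.25.

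**If the full design effect applied to the tests.**
- Standard error too small by 1 - 1/√1.25 = 10.6%.
- Critical value for .0167 is 2.394. In true standard errors this is 2.394/√1.25 = 2.141, so the actual size is .032.
- Three tests: 1 - (1 - .0323)³ = .094 if independent, and at most 3 × .0323 = .097.
- With 12 × .7 = 8.4 per clinic (DE 1.215) the size is .030 per test. With 12 per clinic (DE 1.319) it is .037.

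**What baseline adjustment changes.** The planned tests adjust for baseline, so the design effect that matters is that of the adjusted score. Let r be the within-person correlation and c the correlation of a clinic's effect between rounds. The protocol gives neither. With outcome variance 1 and a baseline slope of about r:

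residual ICC = ICC × (1 + r² - 2rc) / (1 - r²)

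DE = 1 + (m - 1) × residual ICC; actual size = 2 × [1 - Φ(2.394/√DE)]; three-test error = 1 - (1 - size)³ if the tests are independent.

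| r | m | c | Factor on ICC | Residual ICC | DE | Size per test | Three tests, formula | Three tests, simulated |
|---|---|---|---|---|---|---|---|---|
| .6 | 8 | 1 | .16/.64 = .25 | .0073 | 1.051 | .020 | 5.7% | 4.9% |
| .6 | 8 | .8 | .40/.64 = .625 | .0181 | 1.127 | .024 | 7.1% | 6.8% |
| .6 | 8 | .5 | .76/.64 = 1.19 | .0344 | 1.241 | .032 | 9.2% | 9.2% |
| .8 | 10 | .8 | .36/.36 = 1 | .0290 | 1.261 | .033 | 9.6% | 9.4% |
| .8 | 10 | .5 | .84/.36 = 2.33 | .0677 | 1.609 | .059 | 16.7% | 14.3% |

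The last column is from 4,000 simulated null trials per row: 15 clinics, three participant-level ANCOVAs at .0167, one-degree-of-freedom contrasts. Monte Carlo error is about √(.05 × .95/4000) = 0.3 percentage points near 5%. With no clustering the same simulation gave 5.2%.

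**Range over settings at ICC .029.** A second set of simulations started from 12 per clinic with 30% lost by week 48, and used r from .6 to .8. It gave 5.1-5.7% at c = 1, 7.4-8.9% at c = .8, and 10-17% at c = .5. Taking both sets together, family-wise error is about 5%, about 7-9% and about 9-17%. A three-group F test at every time point ran higher at r = .8 with 10 per clinic: 9.8% at c = .8 and 19.4% at c = .5. Analysing baseline-adjusted clinic means kept the error at 4.6-5.7% in every ICC .029 setting of the second set.

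**If the ICC differs** (r = .6, 10 per clinic, c = .5): 6.1% at ICC .01, 10.1% at .029, 15.3% at .05.

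**The case against.** The strongest reply is that the same section does handle clustering. It commits to mixed models with random effects for that purpose, and their contrast is the usual stepped-wedge one and the one that answers the primary objective. On this reading the ANCOVAs are a preliminary step. This stands in part: a reader might infer that the plan ignores clustering altogether, and the text does not support that. But the section calls the ANCOVAs the method of analysis and presents the mixed model as an addition, with no ranking.

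Second, baseline adjustment can remove most of the clinic variation. This also stands: with perfectly stable clinic effects the error stays near 5%. A reader might infer that each test's error is doubled, that the family-wise error is 9.4%, or that standard errors are 11% too small. Those figures hold only if the full design effect of 1.25 carries through to the adjusted test, and depending on r and c the adjusted value can lie below or above it. The protocol offers no evidence that clinic effects stay constant over 48 weeks.

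Third, the section says only that later data are compared with baseline and does not define the group contrasts. Those simulated are therefore assumptions. The .0167 is attached to tests at three time points and does not name the ANCOVA, so the mixed model cannot be said to be tested at some other level. Likewise, no model formula is given, so the missing clinic term is inferred from the sentence that follows.

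Fourth, the ICC is borrowed from diabetes patients in primary care. That limits precision on size, but it is the plan's own figure. A plan that sizes for clustering should also test for it.

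**Conclusion.** The point holds in a conditional form. As worded, the three time-point ANCOVAs ignore the unit of randomisation, and nothing ranks the clustered model above them, so p-values that do not respect clinic could be reported as the primary result. The intended 5% is not assured. How far it is missed rests on the between-round correlation of clinic effects, the within-person correlation and the ICC; the documents give only the last.

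No power cost is put on the correction. A reader might compute one at Time 3 from the 180 × .7 = 126 participants expected at week 48. That applies end-of-study attrition to an interim test and gives no credit for baseline adjustment, so it would mislead.

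**What to change.** Any one of these would do:

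- Name the mixed model as the primary analysis, with a clinic random effect, period effects and small-sample degrees of freedom suited to 15 clinics, and label the ANCOVAs descriptive. Because the inflation comes from clinic effects that shift between rounds, a clinic-by-period random term deserves consideration.
- Keep the tests at Times 3 to 5, but give each baseline-adjusted model a clinic random effect with small-sample degrees of freedom.
- Analyse baseline-adjusted clinic means at each time point, on 13 degrees of freedom for a two-group contrast.

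The particular small-sample correction can be left to the statistical analysis plan; the ranking of the analyses should be stated. The cost is a sentence or two of wording and no new data. Intervals will be wider but valid, and some apparent power will be lost. That is better known before the data are analysed.
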